**Design:**

The intended pilot study is designed as a multicenter randomized controlled clinical trial, comparing the impact of two different time intervals from tooth extraction to initiation of orthodontic space closure on the development of gingival invaginations.

Forty participants, men and women in the age range of 11 to 30 years with orthodontically related indication for tooth extraction in the lower jaw, will be randomized 1:1 in one of two treatment groups. In group A the orthodontic tooth movement into the extraction area will be initiated in a time interval 2 to 4 weeks after tooth extraction. In group B the tooth movement will be initiated in a time interval >12 weeks after extraction. A possible effect of these treatment modalities on the development of gingival invaginations will be documented at the moment of space closure or 10 months +/- 14 days after initiation of space closure respectively, by clinical documentation of the primary (reduced number of gingival invagination) and the secondary endpoint (reduction of the severity of gingival invaginations).

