**Figure 1 F1:**
[figure not shown]
Exemplary illustration of a gingival invagination established after extraction of tooth 16 with subsequent orthodontic space closure.

In retrospective studies several potential risk factors for the development of gingival invaginations were evaluated, namely time from tooth extraction up to initiation of tooth movement, localization of the extraction area, smoking and duration of space closure [2,3,5]. Further, data of an animal experiment [6] suggested that early tooth movement into an extraction site could be beneficial to prevent gingival invaginations, so atrophy of the alveolar process does not proceed.

In this clinical study we try to prove the hypothesis that a timely tooth movement into an extraction area could be beneficial and prevent the development of gingival invaginations.

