## Methods/Design

### Study objectives

The objective of the clinical study proposal will be to investigate the effects of a timely *versus* a prolonged space closure after tooth extraction on the incidence and severity of gingival invaginations. The study will compare two treatment groups: in group A the orthodontic tooth movement into the extraction area will be initiated in a time interval 2 to 4 weeks after tooth extraction. In group B the tooth movement will be initiated in a time interval >12 weeks after extraction. The null hypothesis will be addressed: There will be no difference of both treatment modalities on the incidence or the severity of gingival invaginations.

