### Endpoint - space closure or 10 months +/- 14 days after initiation of space closure

The primary end point of the study is the fulfilled space closure. If the time for space closure of a patient included in our study would exceed 10 months, this could possibly reveal problems in the treatment process. As a consequence an alternative end point was set on 10 months +/- 14 days after initiation of space closure.

This appointment obtains another plaque- and bleeding index, probing depth of the adjacent teeth, stone models, and intraoral photos. Further, the fulfilled space closure, the occurrence of gingival invaginations, their dimension and time from initiation up to space closure will be recorded.

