### Outcome measurements

#### Primary outcome measurement

Primary outcome measurement will be a determination of the number of gingival invaginations at the moment of space closure. A gingival invagination is present, if there is a probing depth of at least 1 mm parallel to the occlusal plain in vestibular or oral orientation measured 2 mm caudal from the crest ‘free gingival margin to junctional epithelium’.

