### Statistical methods

Primary aim of the study is the estimation of the frequency of gingival invaginations under both therapies. In group A the initiation of the orthodontic tooth movement will be performed in a time interval 2 to 4 weeks after tooth extraction *versus* tooth movement initiated in a time interval >12 weeks after extraction (group B). At the endpoints ‘space closure’ or ‘10 months +/- 14 days after initiation of the space closure’, the frequencies of gingival invaginations will be given together with 95% confidence limits. Also the odds ratio for the occurrence of gingival invaginations in both study arms will be calculated together with a 95% confidence interval. Finally, a two-sided Fisher’s exact test will be performed to descriptively compare the rates between treatment arms.

For the secondary aim, the difference in the dimensions of the gingival invaginations according to LC^2^, the median, minimum and maximum values as well as quartiles will be given. For the comparison of the values a two-sided Mann-Whitney-Wilcoxon test will be performed. Also the odds ratio in both study arms will be calculated together with a 95% confidence interval. In the case of an absence of a gingival invagination LC^2^ will be set to zero.

If some patients do not achieve the primary endpoint ‘fulfilled space closure’ and finish the study within the alternative endpoint ‘10 months +/- 14 days after initiation of space closure’ we would excluded these patients for later statistical analysis because they could possibly represent confounders.

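### Excluding randomised patients whose space is not closed by 10 months conditions the analysis on a post-randomisation event, may bias the arm frequencies and odds ratio, and conflicts with the plan's own 10-month endpoint

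*Protocol article*

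**What the plan says.** The protocol article handles the 10-month visit in different ways in different places.

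- **Abstract, Design:** the effect "will be documented at the moment of space closure or 10 months +/- 14 days after initiation of space closure respectively".
- **Endpoint section:** completed closure is the primary end point. Closure taking longer than 10 months might point to treatment problems, and so "As a consequence an alternative end point was set on 10 months +/- 14 days after initiation of space closure". Occurrence and dimension of invaginations are recorded at that appointment.
- **Primary outcome measurement:** the outcome is a "determination of the number of gingival invaginations at the moment of space closure". The 10-month visit is not mentioned.
- **Statistical methods, first paragraph:** "At the endpoints ‘space closure’ or ‘10 months +/- 14 days after initiation of the space closure’, the frequencies of gingival invaginations will be given", with 95% confidence limits, an odds ratio and a descriptive two-sided Fisher's exact test.
- **Statistical methods, last paragraph:** of patients who reach only the 10-month end point, "we would excluded these patients for later statistical analysis because they could possibly represent confounders".

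The Background lists "smoking and duration of space closure" among potential risk factors for invaginations, taken from retrospective studies.

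**The concern.** Randomisation makes the two arms comparable as randomised. Whether a space closes within 10 months of starting is known only afterwards. It may depend on when movement starts, which is the intervention, and it may be related to invagination risk, since closure duration is a suspected risk factor. A variable of that kind is post-treatment, so the stated reason for the exclusion fails. Restricting to closers compares early-start closers with late-start closers, and these need not be the same kind of patient.

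Statistical methods makes estimating the frequency in each arm the primary aim, and Sample size says the data should support the caseload calculation for later trials. A selected frequency would carry into that calculation. The exclusion also discards outcomes that the plan schedules and, in the same section, undertakes to report.

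**Working it through.** **1. Passages side by side.** The Design paragraph of the abstract and the Endpoint section have the outcome documented at closure or 10 months. Recording at 10 months is compatible with later exclusion, so these two sections are not in strict contradiction with it; their data are simply not used. The direct conflict is within Statistical methods: the first paragraph reports at either end point and the last removes everyone who reached only the second. Primary outcome measurement (closure only) agrees with the exclusion, so it must be reconciled too.

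**2. Possible size of the bias.** The documents give no non-closure rate. All shares and risks below are assumptions.

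*Example 1, no treatment effect on invaginations.* Assume 70% of patients close under either timing, 20% close by 10 months only if started early, and 10% never close. Invagination risks are 70%, 95% and 95%.

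- All randomised, either arm: 0.70×0.70 + 0.30×0.95 = 0.775
- Closers, group A: (0.70×0.70 + 0.20×0.95)/0.90 = 0.756
- Closers, group B: 0.70
- Odds ratio A vs B: (0.756/0.244)/(0.70/0.30) = 1.32; the true value is 1

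If the 20% close only when started *late*, the odds ratio is 1/1.32 ≈ 0.75.

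*Example 2, stronger selection.* Shares 60/30/10% and risks 60/95/95%.

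- Closers, group A: (0.60×0.60 + 0.30×0.95)/0.90 = 0.717
- Closers, group B: 0.60
- Odds ratio: (0.717/0.283)/(0.60/0.40) = 1.69

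*A second parameterisation.* Let r be the rate in all randomised, f the share not closed and q the rate among non-closers. The closers' rate is (r − f·q)/(1 − f). Take r = 0.80 in both arms.

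| f in A, B | q in A, B | Closers A | Closers B | Odds ratio |
|---|---|---|---|---|
| 0.10, 0.30 | 1.0, 1.0 | 77.8% | 71.4% | 1.40 |
| 0.10, 0.30 | 0.5, 0.5 | 83.3% | 92.9% | 0.38 |
| 0.20, 0.20 | 0.5, 1.0 | 87.5% | 75.0% | 2.33 |
| 0.10, 0.30 | 0.8, 0.8 | 80.0% | 80.0% | 1.00 |
| 0.10, 0.10 | 1.0, 1.0 | 77.8% | 77.8% | 1.00 |

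The last two rows are the benign cases. In the fourth, non-closers carry their arm's rate and nothing is distorted. In the fifth, share and risk match across arms, so there is no spurious contrast, although both frequencies still sit below the 80% in all randomised.

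**3. Precision (secondary).** Exact enumeration over two independent binomials, counting tables with two-sided Fisher p ≤ 0.05, reproduces all 12 cells of Table 1 at 20 per arm. The 0.05 level is not stated; it is inferred from the 95% intervals and supported by the match. For 1.00 vs 0.70:

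| Analysed per arm | Power |
|---|---|
| 20 | 76.2% (Table 1: 76.2%) |
| 18 | 66.7% |
| 16 | 55.0% |

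Losses of 2 or 4 per arm are assumed.

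**The case against.** **The exclusion follows the outcome definition.** The primary outcome is defined at closure, the Background describes invaginations as following extraction and space closure, and the Endpoint section ranks completed closure first. This stands as an explanation of the rule, and it means that deleting one sentence is not enough. It does not rescue the comparison: an outcome defined only for closers still compares groups selected after randomisation.

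**Treatment dependence is not shown.** This stands. A reader might infer that closure by 10 months is known to differ by arm, or that group B has less time to close. The documents support neither. No closure rate is given, and the 10 months run from initiation of space closure in each arm, so a later start does not shorten the window. Duration of closure is listed only as a *potential* risk factor, so it is also not established that the excluded patients have a different risk.

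**The bias is small beside the imprecision.** Example 1 implies 18 and 14 closers, hence about 13.6 and 9.8 events. The standard error of the log odds ratio is √(1/13.6 + 1/4.4 + 1/9.8 + 1/4.2) ≈ 0.80, so a 95% interval around 1.32 runs from roughly 0.3 to 6. That is true of this pilot. Selection bias of this kind would not shrink in a larger trial that kept the rule.

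**It is a pilot, and power is not the basis of its size.** Sample size says the number was not set mainly on statistical grounds, and Fisher's test is descriptive. The power loss therefore carries little weight. The frequencies do carry weight, because estimating them is the stated primary aim.

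**Conclusion.** The point holds as a possible and avoidable selection bias together with an internal conflict. The exclusion is explicit and its stated reason is wrong, because a post-randomisation event is not a confounder of a randomised comparison. It also discards outcomes that are scheduled to be measured.

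It would go too far to say that the results *will* be biased, or in which direction. With no true effect, the assumed closure patterns in Examples 1 and 2 give spurious odds ratios of about 0.75 to 1.7. The more extreme assumptions in the table, with equal overall rates in both arms, reach 0.38 and 2.33. There is no spurious contrast if non-closers carry their arm's rate, or if their share and risk match across arms. Nothing in the document secures either condition. Loss of precision is a secondary consequence.

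**What to change.** 1. Delete the exclusion sentence at the end of Statistical methods.
2. Amend Primary outcome measurement so that the outcome is assessed at space closure or at the 10-month visit, whichever comes first, in line with the first paragraph of Statistical methods.
3. Define the primary analysis set as all randomised patients with an assessable extraction region, analysed in their assigned arm. The qualifier is needed because Participants removes regions with extraction or healing complications, and extraction follows randomisation.
4. Report by arm the proportion closed by 10 months and the number of regions excluded for complications.
5. Keep the closers-only analysis as a labelled sensitivity analysis.

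The cost is wording: the Endpoint section already schedules the recording at the 10-month visit, and no clinical procedure changes. The downside is that the primary estimate mixes closed and not-yet-closed sites, which matters somewhat given how the Background defines an invagination. The closure proportions and the sensitivity analysis make that mixture visible. Dropouts without a final visit are not solved by this change and still need their own handling.

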## Discussion

This study is a preliminary study targeting on the effect of a timely coordinated space closure after tooth extraction on the development of gingival invaginations. Other factors like extraction technique, treatment mechanics for space closure or patient-related features could also have an impact on their development. As there is no prospective data up to now, this study can only have preliminary character and therefore it is focused on only one potential risk factor. Having this data, it will be possible to plan future RCTs with adequate sample size, focusing on new risk factors identified in this study.

## Trial status

Patient recruitment since 10.12.2012

## Abbreviations

Ref. No.: Reference number; CSSC: Clinical study support core; IMBIE: Institute for Medical Biometry, Informatics and Epidemiology; RCT: Randomized controlled trial.
